### Participant eligibility

We will apply the following criteria to identify suitable patient participants for each aspect of the study**:**informed consentsufficient levels of concentration and English language to complete the required battery of self-report measures with breaks if needed.

These criteria will be determined by the researcher when meeting the participant and in collaboration with the clinical team.

We will exclude:patients whose discharge is planned for before the start of the intervention periodstaff who plan to leave their jobs during the intervention time periodagency workers, other non-permanent members of staff unless they are a regular bank worker or people who work less than 75% of their working week on the ward.

### Site selection and participant recruitment

Thirty-four generic acute mental health wards will be recruited across England and Wales. The sites will be selected across geographically diverse locations and include Greater Manchester Mental Health NHS Foundation Trust where the study is based.

### Recruitment

The baseline data will be gathered after the ward has been randomised. This is not the optimal design as it runs the risk of selection bias and in particular the control wards not being motivated to engage in the intervention. However, it was deemed to be the most practical solution due to difficulties in organising training for all ward staff at the start of the intervention (at least 4 weeks are needed to schedule rosters, backfill ward staff and book suitable rooms) and the importance of recruiting patients just prior to the start of the intervention (so they are exposed to at least some elements of it before being discharged from the ward). In order to circumvent the risks associated with early randomisation, the outcome of the randomisation will only be disclosed to a few key people (see below).

During the ward recruitment period, all staff on the ward and all patients on the ward meeting inclusion criteria will be approached about the study. Researchers will base themselves on the wards during the recruitment periods in order to promote the study and maximise opportunities for recruitment. Staff and patients will be provided with a written copy of the participant information sheet describing the details of the study. Where possible, potential participants will be given at least 24 hours to decide whether or not they would like to participate. However, if a participant wants to take part before this 24-hour window, we will give them the opportunity to do so. In all instances, participants will be provided with the opportunity to read the participant information sheet, be provided with the opportunity to ask questions about the research, and have their questions answered satisfactorily. They will be asked to consent to completing self-reported outcome measures and/or consent to take part in a qualitative interview. The information sheet and consent form will state that their participation is entirely voluntary and that they are free to withdraw from the study at any point. It is likely that most of the patients recruited at baseline will be discharged before the follow-up period. Therefore, follow-up measures will be completed in community settings. Researchers will take a proactive approach to follow-up assessment which will involve multiple attempts to contact people and being flexible with appointment times and locations, including the possibility of conducting follow-ups via email/ Microsoft Teams (staff) and/or phone (staff and patients).

Separate consent will be sought from patients on the ward at 6-month follow-up to complete the Views on Inpatient Care (VOICE; [20]). This is because it is likely different patients who will need to be recruited from baseline given the probability that the same patients will no longer be on the ward. Although participants will not be blind to the treatment condition of the ward, there will be a separate participant information sheet for the VOICE, which will not explicitly refer to the fact that the study is testing the effects of providing psychological therapies on inpatient wards. Potential participants will be informed that the study is assessing patient satisfaction with wards with different compositions of multidisciplinary team members**.**

### Intervention

All patients on the ward during the intervention period will be involved with a stepped model of care intervention at one of three levels. The level the patient receives will be decided by the multidisciplinary ward team, considering the patient’s and carers’ wishes and needs at the time. At Step one, all patients will have a psychological formulation developed by a Band 8a or 8b Health and Care Professions Council registered psychologist in conjunction with the patient or members of the ward team (which will include the person’s named nurse). A formulation provides a framework for bringing together biological, societal, cultural and psychological factors that might be responsible for the development and maintenance of problems and thus facilitate planning and implementing the most appropriate intervention [21]. The formulation will focus on the development or maintenance of difficulties depending on needs of those involved and the information available. No specific therapeutic model is stipulated on the basis that different psychologists may be trained in different approaches and the process of formulating is deemed to be more important than the specific methodology. Discussions arising from the formulation at Step one will determine whether or not the patient would benefit from being offered a Step two or three intervention. To help support this work, all ward staff will undertake a half-day training session at the beginning of the intervention period (ideally within the first two weeks). This initial training session will describe psychosocial models of mental health and the role and process of formulation.

At Step two all qualified nurses will be trained and supervised by a psychologist to deliver guided self-help material of psychological interventions targeting key problem areas for patients (e.g. anxiety management, behavioural activation for low mood, coping with symptoms of psychosis, minimising self-harm behaviours and suicidality). The staff will be provided with guided self-help booklets to use with patients and be requested not to use their own material. Interventions can be delivered in group or one-to-one formats. The level of group versus one-to-one sessions is to be determined in collaboration with senior ward staff. All qualified nursing staff will be trained in the guided-self-help material at the beginning of the intervention (ideally within the first two weeks) and will receive fortnightly supervision slots with the psychologists to support any work they are undertaking.

At Step three, patients who are felt to have needs that cannot be met at Step 2 and who want to engage in psychological therapy will be offered up to 16, one-to-one therapy sessions with the psychologist. These sessions will most likely focus on understanding the reasons for the current or repeated relapses and developing coping tools to address key factors triggering relapse. The length and frequency of each session will be determined on a case-by-case basis taking into account the patient’s needs and wishes, as well as the views of the wider multi-disciplinary team. No model of therapy is specified on the basis that the psychologist may be trained in different approaches and the TULIPS intervention is primarily testing the delivery a psychologically-informed environment as opposed to testing a specific form of therapy. However, the sessions should rate highly on non-specific therapeutic factors and working alliance.

In addition to delivering the stepped model of care, the psychologist will also deliver fortnightly group-based, staff reflective practice sessions of one-hour duration and fortnightly team formulation sessions of one-hour duration. Note that these team formulation meetings are separate and in addition to level one formulations and are about a group of staff coming together to reflect on their current and future work with a patient. Decisions about which patients to discuss during these meetings should be based on staff request. However, the psychologist should ensure that meetings do not focus solely on high risk patients as those with lower risk who are less problematic for staff may be excluded. The psychologist will also attend ward MDT meetings. The number of MDT meetings attended, and frequency will be determined in collaboration with senior nursing and medical staff.

The intervention period will run over a period of 6-months and wards randomly assigned to receive the intervention will employ a Psychologist NHS Band 8a or 8b on the ward for 0.5FTE for 7 months to support intervention delivery.

No restrictions will be placed on other care and interventions that are delivered during the trial, but we will attempt to monitor other interventions delivered to patients including other psychological intervention as part of the patient resource use inventory (see outcome measures section below). We will also record any dedicated psychological resource for both intervention and control wards in the study in terms of whole-time equivalent resource and banding.

### Outcome measures

Co-primary outcome measures have been selected. The first measure is total number of serious incidents (risky behaviours) per ward. We will be collecting serious incidents at baseline, 3-month follow-up, 6-month follow-up and 9-month follow-up. The data will be requested for the prior 3 months and will include incidents that fall into the categories of self-harm and violence (to staff, patients, and others).

All Trusts involved in the study are already required to collect ward level data on serious incidents as part of standard practice. Reporting criteria and procedures for serious incidents will be reinforced by senior managers in both intervention and control wards recruited to the study to sensitise all participating wards to reporting risk. As an additional protection against bias, blind assessors will collate data of staff-reported serious incidents and complete a 25% check across the 34 wards to ensure that they meet well operationalised definitions utilised in our previous research [15, 22].

The second primary outcome measure will be patient well-being as assessed by the Warwick-Edinburgh Mental Well-being Scale (WEMWBS; http://www2.warwick.ac.uk/fac/med/research/platform/wemwbs), which is a patient-reported health measure that will be collated at the individual patient level by blind assessors. The WEMWBS is used widely by IAPT for SMI and previous studies show that it is rated favourably by patients [23].

Despite the argument for the importance of serious incidents, we recognise the equally important value of targeting and assessing patient-reported outcome measures and will therefore measure patient mental well-being.

Other important outcomes to target and assess are distressing mental health symptoms and level of patient social functioning. These will be measured through the Brief Symptom Inventory (BSI; [24]) and Personal and Social Performance Scale (PSP; [25]). Improving these outcomes is not only important for patients and their families, but is likely to reduce length of admission, which in turn has the potential for significant cost savings. A further important outcome is patients’ perceptions of ward atmosphere [7, 11, 26] and previous research has suggested that working with ward staff to help them to deliver more psychologically-informed care can improve patient perceptions of ward atmosphere [27]. Improving patient access to psychological therapies is also likely to have a positive effect on frontline mental health staff who often experience high levels of burnout when working with risky behaviours. Patient and staff perceptions of the ward atmosphere will be assessed using the Views on Inpatient Care (VOICE; [20]) and Views on Therapeutic Environments (VOTE; [28]), respectively.

Staff burnout will be measured using the Maslach Burnout Inventory (MBI; [29]). Additional ward level data, patient resource use, and health-related quality of life measures will support the health economic evaluation.

See Table 1 for further information on who completes which measures in the study and at what time point.

**Table 1 Tab1:** Outcome measures and time-points for collection

**Measures**	**Baseline**	**6 Month** **Follow Up**	**9 Month** **Follow Up**

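### The baseline serious-incident count runs past ward randomisation by an unstated number of weeks, although routine records would let it end at randomisation

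*Protocol article*

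**What the plan says.** All references are to the protocol article.

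- **Outcome measures.** The first co-primary outcome is the number of serious incidents per ward: "We will be collecting serious incidents at baseline, 3-month follow-up, 6-month follow-up and 9-month follow-up". For these collections, "The data will be requested for the prior 3 months". Trusts already hold ward-level incident data as part of standard practice. Senior managers reinforce reporting in intervention and control wards alike. Blind assessors collate the reports and check 25% of them.
- **Recruitment.** "The baseline data will be gathered after the ward has been randomised". The section concedes that this is not the best design and gives two reasons for it: training takes time to organise ("at least 4 weeks are needed to schedule rosters, backfill ward staff and book suitable rooms"), and patients should join shortly before the intervention begins. As mitigation, only a few key people learn the allocation.
- **Intervention.** "all ward staff will undertake a half-day training session at the beginning of the intervention period (ideally within the first two weeks"). Each intervention ward "will employ a Psychologist NHS Band 8a or 8b on the ward for 0.5FTE for 7 months", against a 6-month intervention period.
- **Blinding and Randomisation.** Allocation is hidden from potential participants until baseline measures are complete. The Project Manager and Chief Investigator are among those not blinded.
- **Data analysis.** Ward-level outcomes are analysed by mixed models with a fixed effect for ward gender and a random ward intercept. The sentence about baseline values as covariates stands in the paragraph on individual-level outcomes.

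**The concern.** A look-back of three months from a date after randomisation takes in time after randomisation. No sentence closes the baseline incident window at randomisation, so part of what is called baseline can in principle be influenced by allocation.

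The protocol's two reasons for a late baseline concern staff training and the recruitment of patients who will be exposed to the intervention. Neither bears on a retrospective count from routine records, which can be requested for any dates. For this outcome the weakness is avoidable.

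What is at stake is a co-primary outcome. If recording or behaviour differed between arms in the weeks after randomisation, the baseline comparison of wards would absorb the difference. Any analysis that conditions on the baseline count, or measures change from it, would carry part of it into the estimated rate ratio.

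**Working it through.** **1. The plan's own figure.** The Sample size section gives more than 80% power with 16 wards per arm, means 5.22 and 3.13, Poisson. Two-sided 5% is assumed here; the section states 5% only for the WEMWBS calculation.
- Difference in means: 2.09 / √((5.22 + 3.13)/16) = 2.09 / 0.722 = 2.89; less 1.96 gives 0.93, power 82.5%.
- Log rate ratio: 0.511 / √(1/83.52 + 1/50.08) = 0.511 / 0.179 = 2.86; less 1.96 gives 0.90, power 81.6%.
- Square-root scale: 83.1%.

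The figure reproduces. It uses no baseline count, so this point does not change it.

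**2. How long the overlap could be.** The protocol gives no interval from randomisation to the baseline cut-off. The only related figures are the training lead time (at least 4 weeks) and the target for training (ideally within the first 2 weeks of the intervention). Assume that the lead time starts at randomisation and that the window ends at intervention start:
- training at the very start of the intervention: overlap of 4 weeks or more;
- training at the end of week 2: 4 − 2 = 2 weeks or more.

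An earlier cut-off, or training later than the ideal, shortens these; a longer lead time extends them.

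**3. Share of the window.** Three months is 13.04 weeks; share = gap / 13.04.
- 2 weeks: 2 / 13.04 = 15.3%
- 4 weeks: 4 / 13.04 = 30.7%

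**4. Illustrative shift.** Assume a 20% difference between arms in recorded incidents in those weeks only. The size has no source in the protocol, and the sign could be either. Shift = 0.20 × share.
- 2 weeks: 0.20 × 0.153 = 3.1%
- 4 weeks: 0.20 × 0.307 = 6.1%

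If 5.22 is read as a 3-month mean (the protocol gives no period), these are 5.22 × 0.031 = 0.16 and 5.22 × 0.061 = 0.32 incidents per ward.

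**5. Passage into the treatment effect.** Let b be the weight that the analysis gives to the log baseline count, from 0 (unused) to 1 (full change from baseline). A shift s in the intervention arm's baseline multiplies the estimated rate ratio by about (1 + s)^(−b).
- b = 0: multiplier 1, no effect.
- b = 1, 2 weeks: 1/1.031 = 0.970, or 1/0.969 = 1.032 if the shift is downward.
- b = 1, 4 weeks: 1/1.061 = 0.943, or 1/0.939 = 1.065.

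The planned ratio is 3.13/5.22 = 0.600. At 4 weeks and b = 1 it would be estimated as about 0.600 × 0.943 = 0.566 or 0.600 × 1.065 = 0.639. This is the outer end of the illustration. The protocol does not propose a change-from-baseline analysis.

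**The case against.** The case for leaving the text alone has real force.

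- **Concealment.** Ward staff are potential participants, and allocation is to be hidden from them until baseline measures are complete. By plan, the people whose reports make up the count do not know the arm. This stands, and is the main reason to expect a small bias. It is not complete protection: somebody must arrange rosters and backfill for intervention wards, and blind collation cannot correct a change in what staff choose to report.
- **The model.** The protocol does not name the baseline count as a ward-level covariate. This also stands. The random ward intercept fits an analysis of repeated ward counts, of which baseline could be one, but that is suggestive only; such a term can also serve to absorb overdispersion.
- **Level of detail.** Extraction dates are often left to the full protocol. Here, however, the article does state the window and the order of events, and together they place post-randomisation time in the baseline.

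A reader might infer more than the text supports:

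- *That at least 4 weeks, or 31% of the window, must follow randomisation.* The 4 weeks is time to organise training, not the gap to baseline, and training may fall inside the intervention period.
- *That those arranging training are stated to know the arm.* This is a fair inference, but the Recruitment section promises details of who is told without an explicit list following.
- *That reinforced reporting separates the arms.* It is planned for both.
- *That the psychologist is already on the ward during the baseline window.* The seventh month is not placed, and a visible presence before baseline would sit badly with the concealment rule.

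**Conclusion.** The point holds in a limited form. Read together, the Recruitment and Outcome measures sections make the baseline count of a co-primary outcome include some time after randomisation. The length is unstated: plausibly about 2 to 4 weeks or more (15% to 31% of the window) if the window closes at intervention start, and less with an earlier close.

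The likely bias is modest and its direction unknown. The 3% to 6% shift rests on an assumed 20% arm difference in recording, for which the protocol offers no evidence. The treatment estimate is affected only if the baseline count enters the ward-level model as a covariate or repeated measure; if not, the consequence is confined to the baseline comparison of the arms. It would be wrong to conclude that the co-primary analysis is invalid. The change is still worth making, because it removes an avoidable route to bias at almost no cost.

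**What to change.** In Outcome measures, define the baseline incident count as incidents in the 3 months ending on the ward's randomisation date, taken from the Trust's routine records. Record incidents between randomisation and intervention start separately, using a matched notional start date for control wards so that the interval is defined alike in both arms.

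This takes a sentence or two in the protocol and different dates on the data request. It needs no new data collection and leaves the sample size as it is. The downside is a baseline that ends some weeks earlier and is therefore slightly less recent.

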**Patient Measures**			
Informed consent	x	x (VOICE participants)	
Demographics	x	x (VOICE participants)	
Brief Symptom Inventory (BSI; Derogatis, 1993)	x	x	x
Personal and Social Performance Scale (PSP; Morosini et al, 2000)	x	x	x
Quality of Life (EQ-5D-5L)	x	x	x
Views on In-Patient Care (VOICE; Evans et al, 2012)		x (VOICE participants)	
Warwick-Edinburgh Mental Well-being Scale (WEMWBS; http://www2.warwick.ac.uk/ fac/med/research/platform/)	x	x (including VOICE participants)	x
Health Economic (HE) Measure	x	x	x
**Staff Measures**			
Informed consent	x		
Maslach Burnout Inventory (MBI; Maslach & Jackson, 1981)	x	x	x
Views on Therapeutic Environments (VOTE; Laker et al, 2012)	x	x	x

All outcome assessors will receive training in the outcome measures from the project team and have access to supervision from a clinically qualified investigator during data collection periods. As detailed in the data management section below, all sites will also be subject to data monitoring which will include compliance with completion of outcome measures.

### Intervention dropout and study withdrawal

Withdrawal from the trial will occur if the participant decides to withdraw from the trial for any or no-stated reason, the participant loses capacity to consent during the study and is lost to follow up (unable to contact at six or nine months). However, data collected up until the point of withdrawal from the trial will be retained and included in the analysis. There is no prespecified criteria for withdrawal of the intervention from a cluster, although Step two and three of the intervention may be withdrawn upon patient request and/or if in consultation with the patient, the care team feel that the intervention is causing significant distress.

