**Methods:**

The study is a single blind, pragmatic, cluster randomised controlled trial and will recruit thirty-four wards across England that will be randomised to receive the new intervention plus treatment as usual, or treatment as usual only. Primary and secondary outcomes will be assessed at baseline and 6-month and 9-month follow-ups, with serious incidents on the ward collected at an additional 3-month follow-up.

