### Sample size

The recruitment target is thirty-four wards. Based on a recent survey of acute inpatient wards across the NHS, it is estimated that there will be an average of 24 beds per ward (range 18-30) giving a pool of 816 patients at baseline across 34 wards. Based on the same survey, it is estimated that there will be an average of 25 staff per ward giving a potential pool of 850 staff across 34 wards. Based on trials of psychological therapy in inpatient settings [27, 30] it has been conservatively estimated that recruitment rates for the completion of individual level outcome measures at baseline will be 80% of eligible staff and 50% of eligible patients giving a pool of 680 staff and 408 patients.

For the primary outcome of number of serious incidents on the ward, assuming 5.22 mean number of events in the control arm [31], 16 wards per arm has more than 80% power to detect a reduction in mean number of events to 3.13 (40% relative reduction), assuming a poisson distribution for the outcome. To allow for possible dropout of a ward, we will recruit 34 wards in total.

For the individual level health related primary outcome (WEBWBS) and other individual level secondary outcomes, we used the –clustersampsi- command in Stata. We assume a between group effect size of 0.4 and an intra-cluster correlation coefficient of 0.05. We allow for a baseline-endpoint correlation of 0.3, which we suggest is conservatively low given the short time span between baseline and endpoint. We specified 85% power, 5% significance level, and calculated the average cluster size (i.e. how many participants were required to be recruited in each cluster). The optimal design for these parameters requires 9 participants per cluster. This leads to a total sample size per arm of 153, and 306 for the analysis set. Accounting for attrition of 20%, by making an adjustment to this value, 383 participants are required at baseline. This assumes that attrition is consistent across treatment arms and clusters. Therefore the aim is to recruit 34 clusters with 11 participants in each cluster, giving a total sample size at baseline of 384. Adjustments will be made for additional covariates in order to preserve 85% power against a larger observed ICC value or a weaker observed baseline-endpoint correlation.

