### Data analysis

Analysis will follow intention-to-treat principles: outcome data will be sought and included in the analysis for all patients irrespective of receipt of the intervention during the time scale of the trial. The CONSORT statement for cluster RCT's will be followed. Treatment effects for the cluster (ward) level outcomes will be estimated using appropriate mixed models with a fixed effect for ward gender, and a random intercept for the ward.

Individual (patient/staff) level outcomes measures will be analysed using an appropriate generalised linear mixed model with random intercepts for wards. With the exception of patient ward atmosphere (VOICE), the baseline values of the outcomes can be used as a covariate in the models.

A statistical analysis plan for primary and secondary outcomes, including sub-group analyses will be presented to and agreed with the programme steering group prior to the allocation codes being revealed and commencement of any data analysis. There are no planned interim analyses.

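### Failed contact at six or nine months is classed as withdrawal from the trial, so a patient missed at 6 months may not be sought for the 9-month assessment still due

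*Protocol article*

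**What the plan says.** All references are to the protocol article.

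- **Intervention dropout and study withdrawal** lists the events that make a participant a withdrawal from the trial. The first is the participant's own decision. The rest of the list runs "the participant loses capacity to consent during the study and is lost to follow up". With its defining parenthesis, the last item reads "is lost to follow up (unable to contact at six or nine months"). The wording is mandatory. Stopping Step two or three of the intervention is dealt with separately, so this list concerns leaving the trial.
- The same section then says that "data collected up until the point of withdrawal from the trial will be retained and included in the analysis". It is silent on collection after that point.
- **Abstract, Methods**: "Primary and secondary outcomes will be assessed at baseline and 6-month and 9-month follow-ups". Table 1 schedules the WEMWBS at baseline, 6 and 9 months.
- **Recruitment** expects most patients to be discharged before follow-up and says: "Researchers will take a proactive approach to follow-up assessment which will involve multiple attempts to contact people". It gives no date at which attempts end.
- **Data analysis** states the intention-to-treat aim: "outcome data will be sought and included in the analysis for all patients irrespective of receipt of the intervention".

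**The concern.** Not reaching someone at one visit is a missing-data state. It is not a decision to leave. The list puts the two in one category, and because six and nine months are joined by 'or', a single missed contact at 6 months is enough. A site that followed the text would have grounds not to try again at 9 months.

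Two things are at stake. First, a gap at one visit could become permanent dropout. Patients who are hard to reach after discharge may plausibly differ in outcome from those who are easy to reach, although the article gives no data on this. A 9-month value that was never sought cannot be recovered by any later analysis. Second, refusals and failed contacts would share one label, so a reader of the results could not tell how much loss was by choice.

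The rule speaks of participants, and the Participants section includes staff, so it also reaches the staff measures at 9 months. The other co-primary outcome, serious incidents, is counted per ward and is not affected.

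**Working it through.** **1. The sections side by side.** Take a patient who consents at baseline, is not reached at 6 months and has not asked to leave.

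- Withdrawal section: withdrawn from the trial at 6 months, with data kept up to that point.
- Abstract and Table 1: a 9-month assessment is due.
- Recruitment: several attempts at contact, with no cut-off at 6 months.
- Data analysis: outcome data are sought for all patients, whether or not they received the intervention.

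The first does not fit comfortably with the other three.

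**2. The plan's own figure.** Inputs from Sample size: "We assume a between group effect size of 0.4 and an intra-cluster correlation coefficient of 0.05"; baseline-endpoint correlation 0.3; 85% power; 5% significance (two-sided assumed); 34 wards, hence 17 per arm; 9 participants per ward.

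- Design effect: 1 + (9 − 1) × 0.05 = 1.40.
- Variance of the standardised difference: 2 × (1 − 0.3²) × 1.40 / (9 × 17) = 2.548 / 153 = 0.01665, standard error 0.129.
- Noncentrality: 0.4 / 0.129 = 3.10. Power is 85.2% with a t distribution on 32 degrees of freedom (87.3% with the normal approximation). Eight per ward gives 82.3% under t.
- Analysis set: 9 × 34 = 306. Baseline: 306 / 0.8 = 382.5, rounded up to 383.

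The stated 306 and 383 reproduce.

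**3. What the rule could cost at 9 months.** The 20% attrition has no time point in the article. Placing all of it at 6 months is an assumption, and so is the share of missed patients who could be reached at 9 months.

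- Missed at 6 months: 0.20 × 383 = 76.6, about 77.
- A quarter reachable at 9 months: 0.25 × 76.6 = 19.
- A half reachable: 0.50 × 76.6 = 38.

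Size of a 9-month analysis set and its power (t, 32 degrees of freedom), with 20% missed at 6 months:

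| Further loss by 9 months among those seen at 6 months (assumed) | Rule applied | 25% to 50% of the missed patients reached |
|---|---|---|
| None | 306, 85.2% | 326 to 345, 86.6% to 87.8% |
| 10% | 276, 82.6% | 295 to 314, 84.3% to 85.8% |

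If the share missed at 6 months is varied from 10% to 30% and the reachable share from 0 to a half, the number lost runs from 0 to 0.30 × 383 × 0.50 = about 57.

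**The case against.** The strongest reply is that the article never tells anyone to stop. The sentence on data up to withdrawal is about retaining what was collected, and the passages on conduct of follow-up point towards continued effort. This stands in part. A reader might infer that the protocol ends pursuit of the 9-month outcome as a stated rule, but the documents support only an implication. Still, the limit on retained data has little meaning unless collection ends there, and nothing in the section tells sites to continue.

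Second, the grammar is loose. The 'and' before the last item could join loss of contact to loss of capacity, so that failed contact alone would not be a trigger. That reading is possible but less natural: it leaves the list without a conjunction between its items and makes loss of capacity alone no longer a ground for withdrawal. If it was meant, the sentence still needs rewriting.

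Third, a reader might infer a flat contradiction of the intention-to-treat commitment. The documents do not support that. The clause is "outcome data will be sought and included in the analysis for all patients irrespective of receipt of the intervention", which addresses patients who did not receive the intervention and does not address loss of contact. It is a tension to reconcile.

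Fourth, a reader might take one figure for the data lost as a property of the plan. It is not, because the timing of attrition and the recoverable share are both assumed. Even with the rule fully applied, 20% missed at 6 months and no later loss leave the planned 306.

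Finally, the model used for the two time points belongs to the analysis plan and is no part of this point. The withdrawal rule is different: it is stated in the article, and it governs whether data are collected at all.

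**Conclusion.** The point holds as a defect in a stated rule. On its natural reading, the withdrawal section makes a missed 6-month contact a withdrawal from the trial while the 9-month assessment is still due, and its wording implies, without saying so, that collection then ends. This is in tension with the contact effort, the visit schedule and the intention-to-treat aim.

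The size is uncertain: about 19 to 38 nine-month assessments out of 383 recruited, if 20% are missed at 6 months and a quarter to a half of them are reachable at 9 months, and 0 to about 57 over the wider range. The effect on power is modest, and the sample size needs no correction for this reason. The main reasons to act are possible bias from follow-up that was never attempted and the mixing of refusals with failed contacts.

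**What to change.** Amend the section on intervention dropout and study withdrawal as follows:

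1. Remove inability to make contact from the withdrawal criteria.
2. Record an unreached 6-month contact as a missed assessment.
3. State that the 9-month assessment is attempted for everyone who has not withdrawn. Leave the existing rule on loss of capacity unchanged, and reword the sentence so that it stands clear of the contact item.
4. Report withdrawals and missed visits separately in the participant flow.

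The cost is an amendment of a sentence or two and a few more contact attempts, of the kind the Recruitment section already promises. Sample size and visit schedule stay as they are.
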